### Measures

*Edinburg Postnatal Depression Scale (EPDS)* [38]*.* This self-reported scale consists of 10 items. The participant chooses which of the four possible answers most closely resembles how she felt the previous week. The validity of the scale into Spanish is satisfactory, with a sensitivity of 79% and a specificity of 95.5%. It showed also good reliability with a Cronbach's alpha of 0.87. The scores range between 0 and 30, and results > 13 or < 13 but item 10 positive during pregnancy are considered positive.

*Generalized Anxiety Disorder-2 (GAD-2)*. This is a very quick screening, comprised by two questions strongly related to anxiety disorder symptoms: “Have you felt nervous, anxious or overwhelmed?” and “Have you felt unable to control or stop your worries?”. For this study, answers to each item will be yes/no. This screening tool has shown a good level of sensitivity and specificity in different studies of validation. If the answer is positive to any of the questions (including the Whooley questions, see below), the screening will be positive, and it will be recommended to administer the EDPS.

*State Trait Anxiety Inventory (STAI)* [39]*.* The aim of the STAI questionnaire is to evaluate two independent concepts of anxiety, each with 20 questions. The state dimension evaluates a transitory emotional state, characterised by subjective, consciously perceived feelings of attention and apprehension and hyperactivity of the autonomic nervous system. The trait dimension evaluates an anxious, relatively stable propensity that characterises individuals with a tendency to perceive situations as threatening. The clinical validity of the Spanish scale showed a sensitivity of 0.94 and a specificity of 1. The internal consistency showed a Cronbach's alpha index between 0.83 and 0.90.

*Symptom Checklist-90-R (SCL-90-R)* [40]*.* Questionnaire made up of 90 items that describe a specific psychopathological or psychosomatic disorder. It is divided into somatization, obsession-compulsion, interpersonal sensitivity, depression, anxiety, hostility, phobic anxiety, paranoid ideation, psychoticism and an additional scale. The intensity of each symptom has to be graduated by the subject from 0 (absence) to 4 (maximum annoyance). The evaluation of the Spanish version showed an internal consistency with Cronbach's alpha index of 0.81–0.90.

*Temperament and Character Inventory-Revised (TCI-R)* [41]. This inventory measures 7 dimensions of personality, composed of 4 of temperament (avoidance of harm, novelty seeking, reward dependence and persistence) and 3 of character (self-direction, cooperation and transcendence). It consists of 240 items measured on a 5-point Likert scale. The Spanish version has shown satisfactory psychometric properties, with a Cronbach's alpha ranging from 0.77 to 0.84.

*Usability Evaluation APP-M-health* [42, 43]*.* An abbreviated, translated and modified version, derived from the *'Questionnaire d'expérience utilisateur*' of the Tcha-Tokey et al. (2018) questionnaire has been used. This adapted version can be found in Additional file 1.

*Whooley questions*. This screening consists of two dichotomous questions, as in the case of GAD-2 screening: “Have you ever felt low spirits, depressed or hopeless?” and “Have you often felt that you have lost interest or pleasure in things?” (Answer: yes/no). As mentioned above, if the answer is positive to any of the questions (including the GAD-2 questions), the screening will be positive and it will be recommended to administer the EDPS.

*Pregnancy satisfaction questionnaire* [44]. It is a validated self-completed scale with 28 items that assesses aspects related to four dimensions: equipment, accessibility, organization of the consultation and care and competence of the staff. Each question is measured on a 5-point Likert scale. The questions are written as form that some of them express positive aspects and others negative. Overall satisfaction is defined as the sum of the scores awarded to each of the judgments, divided by 28. A woman is considered satisfied with the follow-up of her pregnancy if she obtains an overall satisfaction > 3, and clearly satisfied if the score is > 4. Cronbach's alpha was 0.92, ranging from 0.71 to 0.93.

### Control group

Pregnant women in the control group will be cited for an extra visit, where they will be given the following scales: STAI, SCL-90 and TCI-R. These women will undergo the usual monitoring of pregnancy control at the center by the midwife, according to the Protocol for Monitoring Pregnancy of the Generalitat de Catalunya [45]. The women will be called to back after 6 weeks to go through the same scales again (except the TCI-R), and the pregnancy satisfaction questionnaire.

### Interventional group: *m-Health*

An *e-health* intervention that will not require advanced qualifications by the nurses involved in the study has been developed. The intervention will consist of an Immersive Virtual Reality (IVR) application with virtual reality goggles Oculus GO, to reduce anxiety during pregnancy. This application lasts 14 min by the use of mindfulness techniques based on breathing, mindfulness and passive muscle relaxation. It consists of three modules that can be chosen completely or separately (Fig. 1).

**Fig. 1 Fig1:**
[figure not shown]
Modules forming the *m-health* virtual reality intervention

The intervention will occur off site using the wireless technology. The aspects that conform this intervention will be: information about the most common perinatal mental health problems, exercises based on attention to breathing (mindfulness—relaxation), 6 weeks of duration, for 14 min a day, knowledge from involved personnel of the number of times the woman has connected and the time she has done the exercise, satisfaction questions to pregnant women after pregnancy, alerts to notify the principal investigator if there is a problem with *e-health*, and, finally, an email address to contact the principal investigator. This intervention has been previously evaluated by a committee of eight experts. These experts gave their recommendations to improve the virtual application. Once the changes were applied, a pilot test was conducted with five women who reported the level of ease of viewing, using and manipulating the application.

Specifically, the virtual application will consist of an adaptation to pregnant women of an application for the general public. The main character that appears in the application is a female avatar, who talks about questions aimed at the target group of pregnant women.

### Consent

Eligible women will be given written information outlining the study purpose, invited to ask questions, and be able discuss their participation with family or care providers.

An informed consent will be obtained from all the participants that agree to participate. Participants will be advised they can withdraw from the study at any time without effect to their care. Women will also be provided with contact details for the research team.

### Data collection and management

Data collection is shown in Fig. 2. Data will be collected at 3 time points; Recruitment 12–14 weeks of pregnancy, pre-intervention and post-intervention. Data will be stored in line with the Mútua of Terrassa ethical procedures considering data storage and security procedures. Participants’ questionnaires will be coded with a numerical identifier and kept separately from any identifiable personal information such as names or addresses.

**Fig. 2 Fig2:**
[figure not shown]
Study design: assessments in the control and intervention groups. Abbreviations: EPDS, Edinburg Postnatal Depression; SCL-90, Symptom Checklist-90; STAI, State Trait Anxiety Inventory; TCI-R, Temperament and Character Inventory-Revised

## Data analysis

### Quantitative data analysis

Data analysis will be primarily descriptive. Participant flow through the study will be presented following Consolidated Standards of Reporting Trials (CONSORT) guidelines [46]. Descriptive data will be presented by means and SDs; medians and ranges; or percentages with 95% confidence intervals (CIs), as appropriate depending on the data being described. The following will be calculated: (1) percentage of participants meeting eligibility criteria, (2) percentage of individuals consenting to the study, (3) percentage entering the randomisation phase, (4) the number of sessions completed by those in the treatment arm, (5) percentage completing the outcome measures at post-treatment follow-up, (6) between group pre-post effect sizes and CIs on the mental health tests. T-tests, Mann Whitney U tests, and or Wilconxon tests will be used, as appropriated. Quantitative analyses will be performed with the program Statistical Package for the Social Sciences (SPSS) v23.0 (IBM company, Chicago, Illinois, USA). A p < 0.05 will be considered statistically significant.

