### Aims

To test the efficacy of a low-intensity intervention led by midwives to improve mental well-being during pregnancy, using an *e-health* application as a support, in primary care centers.

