## Design and methods

This will be a two-arm prospective, randomized, parallel-controlled clinical trial. 70 women will be recruited and screened during their pregnancy. Women showing positive scores in an early mental health screening at weeks 12–14 of pregnancy (screening tests: two Whooley questions, two Generalized Anxiety Disorder-2 [GAD-2] questions, self-administered Edinburg Postnatal Depression [EPDS]) will be randomly allocated to an intervention or control group.

If the answer to all four initial questions is negative, we will consider the screening negative. If the answer is positive to any of the four questions, the screening is positive, and it is recommended to administer the EDPS. EDPS is negative if score < 13 or item 10 is negative. EPDS is positive if score < 13 and item 10 positive or ≥ 13. If the answer is positive to any of the four questions, but the EDPS is between 9–13, they are candidates to enter the study.

The usual monitoring of pregnancy control will be carried out at the center (including anamnesis, blood tests, serology and urine tests, among other assessments), regardless of the group. In a first phase (weeks 12–14 of gestation), the following tests will be performed in both groups: EPDS, State Trait Anxiety Inventory (STAI), Symptom Checklist-90-Revised (SCL-90-R), and Temperament and Character Inventory-Revised (TCI-R). The intervention group will receive the usual mentioned follow-up pregnancy monitoring plus an *e*-*health* (virtual reality) intervention. The control group will receive the usual mentioned follow-up pregnancy monitoring, without the *e*-*health* intervention. In a second phase (6 weeks after), the following assessments will be repeated in both groups: EPDS, STAI, and SCL-90. In the case of the intervention group, a questionnaire on the usability of the technology will also be passed. At the end of the pregnancy all women will receive a questionnaire on their satisfaction with the follow-up of their pregnancy, including questions on equipment, accessibility, organization of the consultation and care and competence of the staff (28 questions in total). Providing a control group that receives the same monitoring control establishes whether the technological low-intensity intervention accounts for the results. The involvement of midwives in collaboration with mental health nurses will maximize the translation of research findings into practice.

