### Outcome measures

The primary outcome measure is possible mental health improvement in pregnant women according to the EPDS, STAI, and SCL-90. Secondary outcome measures will include the TCI-R and the Whooley and GAD-2 questions. Routinary pregnancy monitoring measures will be also evaluated (i.e., anamnesis, blood tests, serology, and urine tests).

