### Inclusion criteria

All women who control their pregnancy in the primary care centers of the Sexual and Reproductive Health Care (ASSIR; *Atenció a la Salut Sexual i Reproductiva*) of Mutua Terrassa, Barcelona (Spain) will be invited to participate. The ASSIR is a support structure for primary care and is located between primary and specialized care, with the aim of promoting, encouraging and coordinating activities for comprehensive sexual and reproductive health care for women. The women must present a positive value in the mental health screening performed at the beginning of the pregnancy (weeks 12–14 of gestation). Women scoring positive (EPS 9–12) will be randomized to either the control or intervention group. The women must be able to have a good verbal and written understanding of Spanish and be ≥ 18 years old.

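### An efficacy trial is given a largely descriptive analysis with unadjusted tests, although baseline scores that would sharpen the between-group comparison are already collected in both arms

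*Protocol article*

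**What the plan says.** The Aims section of the protocol article sets out "To test the efficacy of a low-intensity intervention led by midwives to improve mental well-being during pregnancy". The Hypothesis section expects lower anxiety and depressive symptoms. The Sample and sample size section tests equality of two means with a two-sided two-sample t-test at 5%, 80% power, a difference of 3.5 points and an SD of 4.83, giving 31 women per group.

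The Quantitative data analysis section opens with "Data analysis will be primarily descriptive". Five of the six quantities it lists describe eligibility, consent, randomisation, sessions completed and follow-up completion. Only item (6), "between group pre-post effect sizes and CIs on the mental health tests", concerns outcomes. On testing it says "T-tests, Mann Whitney U tests, and or Wilconxon tests will be used, as appropriated", with p<0.05 throughout.

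Baseline data exist. Under Design and methods, "In a first phase (weeks 12–14 of gestation), the following tests will be performed in both groups: EPDS", together with STAI, SCL-90-R and TCI-R; later, "In a second phase (6 weeks after), the following assessments will be repeated in both groups: EPDS, STAI, and SCL-90". Under Outcome measures, "The primary outcome measure is possible mental health improvement in pregnant women according to the EPDS, STAI, and SCL-90". Entry depends on one of these scales: "Women scoring positive (EPS 9–12) will be randomized to either the control or intervention group".

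**The concern.** Two things do not fit together. First, a powered efficacy hypothesis calls for a named between-group contrast as the main result. The analysis section presents the work as mainly descriptive and leaves the choice of test open. Because Mann-Whitney is already listed for independent groups, a separate Wilcoxon test is most naturally read as the paired signed-rank test, that is, a pre-post test within an arm. The section does not say what such a test would be used for.

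Second, all three primary scales have a baseline in both arms, and none of the named tests uses it. In a trial of about 31 to 35 women per arm, chance baseline differences can be material, and a prognostic baseline would narrow the confidence interval at no cost. At stake are precision and a clear statement of which comparison carries the efficacy claim. The validity of the between-arm test is not at stake.

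**Working it through.** **Inputs from the protocol.** Difference 3.5, SD 4.83, two-sided alpha 0.05, 31 per arm (Sample and sample size); EPDS entry range 9–12 (Inclusion criteria; Recruitment protocol and randomization procedure).

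**Assumed, because the protocol does not give them.** Baseline–follow-up correlation r of 0.3 to 0.7 (0.5 to 0.7 for EPDS before selection); EPDS SD before selection of 4.0 to 4.83; EPDS mean before selection of 6 to 10.

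**1. The plan's own figure.** Standardised effect d = 3.5/4.83 = 0.725. The noncentral-t calculation gives 30.9, so 31 per arm, with power 0.802 at 31. The stated group size reproduces.

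**2. Adjustment where the baseline is not range-restricted.** ANCOVA multiplies the SD by √(1−r²); a change score multiplies it by √(2(1−r)). The EPDS-based d of 0.725 is borrowed here for STAI and SCL-90.

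| r | ANCOVA effect, d/√(1−r²) | ANCOVA power | Change-score effect, d/√(2(1−r)) | Change-score power |
|---|---|---|---|---|
| 0.3 | 0.725/0.954 = 0.760 | 0.84 | 0.725/1.183 = 0.612 | 0.66 |
| 0.5 | 0.725/0.866 = 0.837 | 0.90 | 0.725/1.000 = 0.725 | 0.80 |
| 0.7 | 0.725/0.714 = 1.015 | 0.98 | 0.725/0.775 = 0.936 | 0.95 |

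Unadjusted power is 0.80 in every row. If the pre-post wording of item (6) means change scores, power at r = 0.3 falls below the planned 80%.

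**3. EPDS after selection on 9–12.** Four equally likely scores have variance 1.25 (SD 1.12). The share of follow-up variance explained by baseline is r²·1.25 / (r²·1.25 + SD²(1−r²)).
- Low end, r = 0.5, SD 4.83: 0.3125/(0.3125 + 17.497) = 1.75%.
- High end, r = 0.7, SD 4.0: 0.6125/(0.6125 + 8.16) = 7.0%.

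So the gain is about 2–7% of variance. With d = 0.725, power moves from 0.80 to 0.81–0.83.

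**4. Does selection bias the between-arm test?** Trials with 31 per arm, selection on 9–12, SD 4.83, a mean before selection of 6 or 8 and r of 0.5 or 0.7 were simulated, 4,000 per setting. With no effect, the mean between-arm difference was about 0 and the type I error 4.4–5.6% for the follow-up t-test, the change-score t-test and ANCOVA alike. With a true difference of 3.5, all three recovered about −3.5 with almost equal power (0.88–0.90 at r = 0.5; 0.97–0.98 at r = 0.7).

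**5. Within-arm change with no treatment effect.** The expected fall is (1−r) × (mean of selected women − mean before selection). The table covers SD 4.0–4.83 and r 0.5–0.7, with a paired t-test at n = 31.

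| Mean before selection | Fall, points | Significant at 5% |
|---|---|---|
| 6 to 8 | 0.7–2.1 | 20–90% |
| 9 | 0.4–0.7 | 10–19% |
| 10 | 0.1–0.2 | about 6% |

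**The case against.** The strongest reply is that nothing here is invalid. The unadjusted t-test is unbiased, holds its error rate and matches the sample-size calculation. Covariates and the analysis model are often left to a separate analysis plan, which is not shown. The protocol also does state a between-arm contrast: the null hypothesis in the sample-size section compares two means, item (6) is between groups, and Design and methods relies on the control group to attribute the result.

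Most of that stands and sets the weight of the point. It does not remove it. The analysis section is not silent: it names its tests, none of them adjusted, and applies a descriptive label that clashes with the stated aim.

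Four stronger readings are tempting, and the documents do not support them:
- **Selection on EPDS biases the trial and ANCOVA cures it.** It does not (step 4). Selection is in fact why adjustment gains little on EPDS.
- **Within-arm improvement will be presented as efficacy.** The Wilcoxon listing permits a within-arm test, but nowhere is such a test said to count as evidence. A false-significance rate of 20–90% also needs a mean of 6–8 before selection. EPDS is given only after a positive Whooley or GAD-2 answer, so the relevant mean may be higher, and at 9–10 the rate is about 6–19%.
- **Effect sizes will be inflated by the narrow baseline SD.** The protocol names no standardiser.
- **Power rises to 0.98 for the trial.** That figure belongs to an unrestricted scale with r = 0.7. The protocol gives no effect, SD or correlation for STAI or SCL-90.

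**Conclusion.** The point holds as a weakness of efficiency and pre-specification that should be corrected. It is not an error that invalidates the trial. The descriptive label does not fit the efficacy aim and the powered two-group test, and the named tests leave already collected baseline information unused. For STAI and SCL-90, adjustment would raise power at 31 per arm from 0.80 to between 0.84 and 0.98, provided that r lies between 0.3 and 0.7 and that the standardised effect resembles the 0.725 planned for EPDS. For EPDS the precision gain is about 2–7% of variance. On every scale, adjustment also deals with chance baseline imbalance. The caution about within-arm tests is conditional: it matters only if such tests are run and read as evidence, and its size depends on an EPDS mean that the protocol does not give.

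**What to change.** Amend the Quantitative data analysis section in three places.

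1. State that efficacy rests on the between-group difference at the post-intervention assessment, estimated by ANCOVA with a 95% CI for EPDS, STAI and SCL-90, each adjusted for its own baseline. This model would replace the open list of tests as the efficacy analysis; it does not settle how three primary scales share the 5% level, which is a separate question.
2. Confine the descriptive label to items (1)–(5).
3. State that any within-arm pre-post test is descriptive and is not evidence of efficacy, because women enter on EPDS 9–12 and may improve without treatment.

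The cost is wording only. The baselines are already scheduled in both arms, the named software fits the model, and the sample size need not change. The amendment should be dated before outcomes are compared between arms.

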### Ethical approval

The research protocol has been reviewed and received approval from the Drug Research Ethics Committee (CEIM; Comité de Ética de la Investigación con medicamentos, CEIM) from Mútua Terrassa (02/2018). The study will be conducted in accordance with the principles of the Declaration of Helsinki (World Medical Association Declaration of Helsinki, 2001) and its later amendments (revised in 2013), and according to the Regulation UE2016/679 of the European Parliament and of the Council of 26 of April de 2016 on the protection of individuals regarding the processing of personal data and the free movement of data.

## Discussion

This proposal addresses a pioneering low-intensity intervention through IVR focused on pregnant women with anxiety and depression problems to improve their mental quality, from the initial stage of pregnancy. This proposal will be carried out in different primary care centers in Catalonia, Spain. The protocol tests the effectiveness of an evidence-based intervention (*e*-*health*), in this case led by midwives and specifically designed in this study for pregnant women, to improve maternal and perinatal mental health problems during pregnancy. The key outcome is to optimise the mental health of pregnant women, promoting normal childbirth and indirectly reducing the burden on the health system.

The proposed protocol evaluates an innovative program that integrates evidence and is feasible in clinical practice. First, it uses a proven intervention in general samples that combines evidence-based strategies with comprehensive knowledge of mood disorders to provide mental health support [32, 35]. Second, it offers home-based intervention, thereby improving accessibility, timeliness, and flexibility for pregnant women. Third, the intervention does not focus on psychopathology and mental problems per se; but strengthens and supports women’s peace of mind, through mindfulness techniques based on breathing, mindfulness and passive muscle relaxation. And fourth, but not least, this intervention is led by midwives, which makes it interesting, as it reduces the health pressure on other professionals to deal the mental problems of pregnant women in the early stages of pregnancy, improving their overall well-being, and requiring less medical attention and referrals to specialists for these issues. The results of this study will contribute to reducing anxiety and depression in pregnant women, in a very simple way, by promoting effective emotional care in the prenatal period by midwives.

What this study can bring to the treatment of anxiety and depression in pregnant women using this virtual reality technology will help to improve the overall therapeutic approach to pregnant women, so that this low-intensity intervention can be incorporated systematically into primary care consultations. Addressing mental health in pregnant women is a fundamental approach to preserve a peaceful pregnancy, free of stress and mood disorders that can affect the fetus and its birth, thus reducing postpartum problems for both the child and the mother and complications for normal infant care.

All this leads us to speak of an increase in the quality of life (QoL) of pregnant women, and of their postpartum period, providing strategies that can help them not only during pregnancy but also afterwards. All this will always translate into an improvement in the upbringing of their children.

The study is expected to take three years. The first two months will be required to hire and train staff. Recruitment will then commence and continue for 24 months. In year 3 we will complete data analysis, reporting and prepare publications and refine resources developed in the project.

In summary, we consider that our project provides very innovative elements that can improve QoL of pregnant women, providing mental resources for their future as mothers. The use of new technologies (IVR) also makes this initiative an attractive project and easy to implement in the future, through the platform used or others. The involvement of midwives in collaboration with mental health nurses will maximize the translation of research findings into practice.

